## Abstract

**Background:**

Inequalities exist in uptake of bowel cancer screening in England with low uptake in areas with high deprivation and amongst certain ethnic and religious groups. Individuals from these groups are more likely to receive a late diagnosis of bowel cancer. Uptake in Muslim communities, for example, has been shown to be lower than in the general population. Culturally adapted interventions are needed to address these inequalities. This feasibility study aims to assess the acceptability and accessibility of an educational faith-placed bowel cancer screening intervention in the East of England, alongside its impact on bowel screening uptake. It was developed by the British Islamic Medical Association in partnership with community stakeholders and professionals.

**Methods:**

Ethical approval was granted on the 27 October 2021, REC reference number 21/EE/0231. A two-group non-randomised feasibility mixed methods study will be conducted, using surveys, focus groups and semi-structured interviews. Participants eligible for bowel screening will be recruited through local mosques and community venues. We aim to recruit 100 participants to the intervention group and 150 to the comparison group (not receiving the intervention). Intervention group participants will complete a survey at baseline, post-intervention and at six-month follow up. Comparison group participants will complete a survey at baseline and at six-month follow up. Outcomes will include: intention to take up screening; actual screening uptake; knowledge, attitudes, barriers and facilitators towards screening. Regional screening hub records will be used to ascertain actual screening uptake at six-month follow-up. Quantitative survey data will be summarised using descriptive statistics (e.g., proportion), and exploratory univariate analysis will be undertaken (e.g., chi-squared test). Two focus group interviews will be conducted with intervention group participants (with up to 16 participants). Semi-structured interviews will be conducted with 10 clinicians delivering the intervention to explore the acceptability of the intervention, training, and delivery. All qualitative data will be subject to a general inductive analysis.

**Discussion:**

The findings will inform how faith-placed interventions can be implemented to increase uptake of bowel cancer screening, and potentially other health promotion programmes, to address health inequalities in ethnically diverse communities in England.

## Introduction

### Background

Screening can save lives and improve quality of life through early identification of a condition. It can also reduce the chance of developing a serious condition or its complications [1]. In England, for over 450,000 people a year, screening produces results that lead to further tests or treatments, with cancer screening programmes preventing 9,000 deaths per annum [2]. Inequitable access to healthcare and preventive services such as screening can lead to significant, avoidable disparities in health outcomes for some groups in society. Ethnicity is not well recorded in screening data, however studies and surveys have shown lower uptake of screening amongst ethnically diverse groups [3–7]. Screening services also consistently underserve low-income groups, who carry a disproportionate cancer burden in England [8–10].

Bowel cancer screening aims to identify cancer early, allowing treatment to be given before it can progress, and improve health and survival outcomes. More than 9 in 10 people survive bowel cancer for five years or more when diagnosed at an earlier stage, compared to 1 in 10 when diagnosed at a late stage [11].

On average around 64% of people took up the offer of bowel cancer screening in England in 2019/20 [12]. However, take-up is much lower in some groups including those in areas of high deprivation and in ethnically diverse communities. There are important variations in the uptake of bowel cancer screening by ethnic groups and religion, with lower uptake in Muslim and South Asian groups, s as compared to those who identified as White and Christian [13]. Emotional barriers such as fear, embarrassment and anticipated shame, as well as low perceived risk, might contribute to explaining lower screening coverage for some ethnic minority communities, such as low uptake of cervical cancer screening amongst ethnic minority women [14]. In addition, people from ethnically diverse backgrounds are more likely to receive a late diagnosis of bowel cancer [15].

The disparities identified in a Health Equity Audit conducted in 2020 by Public Health England, East of England (unpublished) were consistent with these statistics. For example, the audit found that for GP practices in the East of England, every 1% increase in deprivation (indicated by the Income Deprivation Affecting Older People Index) was associated with a 0.79% decrease in bowel screening uptake. Every 1% increase in non-white ethnicity was associated with a 0.16% decrease in bowel screening uptake. It also highlighted that men and people with disabilities were also less likely to access bowel cancer screening.

The East of England includes localities that have both a high proportion of Muslim residents [16] and low uptake of bowel cancer screening and areas with high levels of deprivation [17]. Culturally adapted interventions within faith settings may improve participation in cancer screening and help to address health inequalities [18–22]. A better understanding of both screening uptake and screening outcomes, analysed by ethnicity and by religious groups (acknowledge that there is likely to be overlap) has the potential to inform more targeted education and informed choice strategies [13].

Culturally sensitive interventions are needed to inform communities with low screening uptake about the need for screening and to overcome barriers such as disinformation, religious objections and cancer fatalism [13, 23, 24]. The British Islamic Medical Association [BIMA] screening intervention, which received a 2019 Royal Society for Public Health: PHE commendation [25], was designed to address this need.

Public Health England, alongside community stakeholders, identified Luton and Peterborough (East of England, UK) as areas that could benefit from the intervention based on bowel cancer screening uptake, levels of deprivation, and ethnic diversity of the populations. The proposed study will determine the feasibility of the intervention.

### The intervention

The BIMA cancer screening intervention uses an adapted presentation slide deck from Cancer Research UK, a national cancer charity. These slides are very lightly modified. This includes having a single slide to motivate attendees through the Islamic injunction to uphold good health. It includes graphics that are tailored to Muslim culture (i.e. women wearing hijab). A slide with publicly available local data that contextualises the shortfall in cancer diagnosis and survival in the mosque community has also been added. The rest of the slides are unaltered and provide a one-hour group education session on bowel cancer screening. This covers screening benefits and harms, how to complete the test, and is followed by a question-and-answer session.

The planned intervention outlined in this protocol will be delivered by local, trusted, senior clinicians who are known to the community. The benefit of this approach will be considered as part of the study.

This innovative conceptual framework positions the intervention as ‘faith-placed’, rather than ‘faith-based’. While there are benefits to ‘faith-based’ interventions there are also risks and ethical considerations [23]. Faith-placed interventions aim to use faith settings such as mosques to target specific communities, without co-opting religious and health messaging [26]. Given the importance of family units in some Muslim cultures, Muslims may value family or community-based approaches to health improvement [27]. This study will therefore also aim to include relevant family and community members. As mixed-gendered groups may limit participation from these communities, we will have gender concordant groups, with male and female groups to be delivered by male and female clinicians respectively. Face-to-face delivery in the community (for example at the mosques after Friday prayers) will be the preferred mode of engagement.

However, as an alternative method of delivery, participants will be offered the option to access the intervention virtually due to the current COVID-19 pandemic restrictions (at the time of planning the feasibility study). This will be offered as a recorded information session with a platform for asking questions or as a live online meeting (via Zoom or Microsoft Teams) and will also serve to include groups which may have an affinity to a faith sensitive intervention but have access issues to the mosque space.

There is already tentative evidence suggesting the potential effectiveness of this approach. A cancer screening promotion event was delivered across 39 faith venues for the Muslim community in 2019. A survey was conducted before and immediately after the event (on the same day). A small number of those who attended the event completed the surveys, (166 of the 900, 18%). Within this group, self-reported intention to take up screening increased from 38% prior to receiving the information to 90% after the event [28]. Further and comprehensive evaluation is now required to establish the acceptability and effectiveness of the intervention to inform approaches to further roll-out.

The findings of this feasibility study will be of regional and national relevance to the implementation and uptake of bowel screening in culturally diverse groups. It is anticipated that if the approach is successful in establishing the feasibility, acceptability, and an increase in screening uptake, the next step would be wider trial rollout in other areas in England where the same issues of deprivation and health inequalities apply within the region.

## Aim and objectives

### Aim

To carry out a feasibility study to assess the acceptability and accessibility of an educational faith-placed bowel cancer screening intervention in the East of England, alongside its impact on bowel screening uptake.

### Objectives

Assess knowledge, attitudes, and behaviours to bowel cancer screening at baseline, post-intervention (intervention group only) and at six-month follow-upAssess intention to undertake screening, as well as validated screening uptake:
Self-reported intention to undertake bowel cancer screeningNumber/ proportion of participants requesting a bowel cancer screening kitNumber/ proportion of participants returning a bowel cancer screening kitUnderstand the feasibility, accessibility, and acceptability of the intervention for participants and for health professionals delivering the interventionIdentify barriers and facilitators that might impact uptake of bowel cancer screening

## Methods

The study was granted ethical approval on the 27 October 2021, REC reference number 21/EE/0231. The study flow chart is available in S1 File.

## Study design

This study will be a two group, mixed methods non-randomised feasibility study. S1 Fig below summarises the study design.

### Study components

The intervention will be evaluated through a mixed-methods approach in line with the Medical Research Council framework for process evaluations [29]. There will be two main elements to the evaluation:

Phase 1: Outcome evaluation

1. **Participant surveys** completed by those receiving the intervention and by those in the comparison group (not receiving the intervention)

Phase 2: Process evaluation

2. **Focus groups** with participants receiving the intervention3. **Semi-structured interviews** with health professionals delivering the intervention

#### Outcome evaluation

In phase one, intention to take up screening will be assessed through a self-reported survey completed at baseline, a post-intervention survey completed immediately after, or within 5 days of, receiving the intervention (intervention group only), and at six-month follow up (intervention and comparison group). A six-month interval was chosen to give the participants sufficient time to request and complete the test while keeping the attrition associated with longer follow-up to a minimum. A larger number of comparison group participants is planned as, based on the delivery of the intervention, recruitment to the comparison group is likely to take less resource than for the intervention group.

At six-month follow up, participants in both groups will be asked if they have requested a faecal immunochemical test (FIT) screening kit, and if they have completed and returned the test (if eligible for screening during the study period).

The Eastern Bowel Cancer Screening Hub will be asked to run a report at six-month follow up to identify participants in study and comparison groups who have requested and/or returned a kit. This will validate participant self-reported data.

#### Process evaluation

In phase two, participants will be invited to attend a focus group to assess the feasibility and acceptability of the intervention. Two focus groups will be conducted with a maximum of 16 people who have received the intervention (6–8 in each focus group). These will take place post-intervention.

Semi-structured interviews with clinicians and other health professionals delivering the intervention (10 clinicians) will be carried out to determine the feasibility and acceptability of the intervention from their perspective. This will include the process of recruiting and training clinicians to deliver the intervention with their communities.

## Participants and sample size

This study will be conducted with four groups of participants:

Individuals and/or their family members/carers identified through mosques/community groups **receiving the intervention**Individuals and/or their family members/carers identified through mosques/community groups **not**
**receiving the intervention** as a comparison groupIndividuals who attend the intervention session, and provide consent to be contacted to be invited to participate in **focus groups**Clinicians/other health professionals recruited to deliver the intervention participating in **semi-structured interviews**

### Inclusion and exclusion criteria

#### Intervention and comparison groups

Inclusion criteria.

Individuals aged 56 years and over (in line with the National Bowel Cancer Screening Programme eligibility, 56 was the minimum age for inclusion in the screening programme at the time of protocol development) [30]Individuals aged under 56 years participating on behalf of a friend/relative/someone they provide care for who is aged 56 years and over. The justification for this is that a member of the Mosque or Muslim community may be living with or caring for someone who is eligible for bowel cancer screening, and so can attend on their behalf. The surveys will capture whether they are responding on behalf of someone elseUse of English as a first languageUse of another language (including Bengali and Urdu) if translation support is available

Participants who require support with translation will be encouraged to ask family members where possible; alternatively, community volunteers will also be available to support participants with the completion of the relevant surveys.

*Exclusion criteria*.

Individuals with a recent bowel cancer diagnosis and/or currently undergoing treatmentAged under 56 years old (if not representing an individual who meets the eligibility criteria)Use of a language for which support from family members and/or community volunteers cannot be found

Feasibility studies do not include formal sample size calculation [31]. As a feasibility study, a sample of 250 participants will be obtained consisting of 100 in the intervention group and 150 in the comparison group. As well as being a pragmatic sample size, this will provide a 95% confidence interval for the proportion of participants in the intervention group who request and/or complete and return a bowel screening kit to an accuracy of ±0.1 and for the participants in the comparison group to an accuracy of ±0.08. Recruitment rates and baseline to 6-month follow-up percentage attrition will be estimated for the two groups. The effects sizes for the differences in proportions between the two groups will give an estimate of the sample sizes required in a future definitive study.

All participants attending the intervention session will be asked if they would be willing to participate in a focus group. We will conduct four focus groups, with 6–8 participants in each (total of 32 participants, at most). We will also conduct semi-structured interviews with each of the clinicians involved in the delivery of the intervention. It is anticipated that this will be with 10 individuals.

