## Data analysis plan

### Phase 1: Outcome evaluation

Analysis will be undertaken comparing responses between the intervention group and the comparison group using SPSS. As the primary focus in a feasibility study is on the methods for dealing with the feasibility objectives rather than statistical testing [31] results will be presented using descriptive statistics (e.g., mean, proportion) and associated 95% confidence intervals. In addition, to gain further insight into an appropriate sample size for a definitive study, exploratory univariate statistical analyses (e.g., t-tests, chi-squared test) will be performed. At baseline we will compare demographic data and eligibility for bowel screening to determine differences in baseline characteristics between the intervention and comparison groups. This will inform our interpretation of any differences in outcomes and enable us to identify demographic and eligibility differences in those who chose to take up the intervention compared to those who did not. Likert Scale responses to questions assessing knowledge, attitudes and intention to take up screening will be gathered at baseline (both groups), post-intervention (intervention group only) and at 6-month follow-up (both groups). This will enable us to compare understanding of screening between groups at baseline and 6-month follow-up, and, for the intervention group, short-term changes in understanding following the intervention.

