## Discussion

### Value of the intervention

Evaluating this intervention is important because it will contribute to the evidence-base for culturally adapted interventions and inform adaptations. The current lack of evidence is a barrier to implementation and the sharing of good practice that could help address health inequalities.

If the research shows that the intervention increases screening uptake in those who receive the intervention, compared with those who do not, and participants find it acceptable and accessible, this will inform a wider roll-out of the intervention. This will result in more people benefiting from the intervention and the research.

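### The definitive study's sample size is to be estimated from an observed between-group difference that is imprecise (about ±0.13) and not randomised; it should rest on a prespecified minimum important difference

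*Protocol article*

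**What the plan says.** The protocol article, under Participants and sample size, plans that "a sample of 250 participants will be obtained consisting of 100 in the intervention group and 150 in the comparison group". It gives the precision of each group's proportion separately. For the intervention group this is the proportion who "request and/or complete and return a bowel screening kit to an accuracy of ±0.1". The corresponding figure for the other group is ±0.08. The paragraph ends by looking ahead to the next trial: "effects sizes for the differences in proportions between the two groups will give an estimate of the sample sizes required" there.

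The Data analysis plan (Phase 1) restates that purpose: "to gain further insight into an appropriate sample size for a definitive study, exploratory univariate statistical analyses (e.g., t-tests, chi-squared test) will be performed". The same section promises descriptive statistics with 95% confidence intervals, and a baseline comparison of the groups to help interpret outcome differences. It names no adjusted estimate of the difference.

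On how groups arise, Sampling approach and recruitment says that community leaders help decide which mosques deliver the intervention and which recruit comparison participants. Attenders at either kind of venue may choose the other group. The possibility of bias is acknowledged there.

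Two further places refer to an effect on uptake. The intervention section says: "if the approach is successful in establishing the feasibility, acceptability, and an increase in screening uptake, the next step would be wider trial rollout". The Discussion (Value of the intervention) begins a sentence "If the research shows that the intervention increases screening uptake in those who receive the intervention, compared with those who do not", adds acceptability and accessibility, and says that this would inform wider roll-out.

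**The concern.** The precision statement covers one quantity and the planned use relies on another. A single proportion known to ±0.1 or ±0.08 says little about how well the difference between two such proportions is known. Required sample size varies roughly with the inverse square of the difference, so a modest error in the difference becomes a large error in the size.

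The difference is also a non-randomised contrast. People who choose to attend a talk on bowel screening may already be readier to be screened, and venues picked by community leaders may differ in other ways. A definitive study sized on this figure could be much too small or needlessly large, and nothing in the sample-size paragraph warns of it.

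**Working it through.** **Inputs from the protocol article.** n = 100 (intervention) and 150 (comparison). Stated half-widths are 0.1 and 0.08. Minimum venues across the two towns are 4 for the intervention and either 4 or 8 for comparison, depending on how the wording on mosques and community groups is read.

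**Assumptions, not in the document.** True uptake rates, attrition and ICC. The article says only that national uptake is about 64% and that uptake is lower in the target groups.

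**1. The stated figures.** Half-width = 1.96·√(p(1−p)/n) at p = 0.5.
- n = 100: 1.96·√(0.25/100) = 0.098, stated as ±0.1.
- n = 150: 1.96·√(0.25/150) = 0.080, stated as ±0.08.

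Both reproduce.

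**2. The difference, for which no figure is stated.** Half-width = 1.96·√(0.25/100 + 0.25/150) = 0.127.
- With assumed losses of 20%, 30% and 40% in both groups (80/120, 70/105, 60/90): ±0.141, ±0.151, ±0.163.

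**3. Sensitivity to clustering by venue.** Design effect = 1 + (m−1)·ICC, with equal venues: m = 25 for the intervention, and m = 37.5 (4 venues) or 18.75 (8 venues) for comparison. No attrition.

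| Assumed ICC | Design effect, intervention | Design effect, comparison (8 / 4 venues) | Half-width (8 / 4 venues) |
|---|---|---|---|
| 0.01 | 1.24 | 1.18 / 1.36 | 0.139 / 0.144 |
| 0.05 | 2.20 | 1.89 / 2.83 | 0.182 / 0.198 |

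**4. What this does to the sample size.** For 60% v 50%, two-sided 5%, 80% power, no clustering:

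n = (1.96·√(2·0.55·0.45) + 0.842·√(0.6·0.4 + 0.5·0.5))² / 0.1² = (1.379 + 0.589)² / 0.01 ≈ 387 per arm.

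From a 50% comparison rate, the same formula (rounded up) gives 1,565 per arm for an observed difference of 5 points, 388 for 10, 170 for 15 and 93 for 20. All four lie inside the 95% interval around an observed 60% v 50%, which is 0.10 ± 0.125, or −0.025 to 0.225. At the lower limit no size can be computed.

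**5. How often the result would mislead.** Every possible outcome of 100 v 150 is weighted by its binomial probability, and the size is recomputed from the observed rates.

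| Assumed truth | Needed per arm | Under half | Over double, or no finite size |
|---|---|---|---|
| 60% v 50% | about 387 | 26% | 33% |
| 50% v 40% | about 388 | 26% | 33% |
| 70% v 50% | about 92 | 9–11% | 17% |

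At 60% v 50% the middle half of the implied sizes is about 185 to 1,200 per arm. The observed difference is zero or negative in about 6% of studies. The range in the last row reflects the choice between pooled and unpooled formulas.

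**6. Confounding.** Its size cannot be computed from the document. It comes on top of the sampling error above.

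**The case against.** The wording is softer than a mechanical rule. The article speaks of an estimate and of further insight, labels the tests exploratory, promises 95% intervals, and makes acceptability and accessibility the primary outcomes. It admits possible bias, explains why randomisation was not used, and plans a baseline comparison. A minimum important difference or progression criteria may also sit in a fuller document that is not shown, so their absence is not held against the plan. All of this stands. It does not remove the explicit sentence naming the observed differences as the source of the sample size. Reading the interval instead of the point estimate would not rescue that use, because in the 60% v 50% example the interval includes zero. A baseline table informs interpretation but does not adjust the difference.

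A reader might infer that an observed increase in uptake is a go/no-go trigger for roll-out, and then criticise the study for low power (about 34% for a 10-point effect). The documents do not support that. Both passages on next steps are anticipatory, list uptake jointly with feasibility, acceptability or accessibility, and attach no test or threshold. One speaks of further trialling and the other only of informing roll-out.

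A reader might also quote implied sizes above 13,000 per arm as the 90th percentile. That figure depends on counting zero and negative differences as infinite. Among finite results the 90th percentile is about 2,900.

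**Conclusion.** The point holds for sizing the definitive study. The per-group precision figures are correct, but the quantity the plan intends to use is known only to about ±0.13 at best, and to about ±0.14 to ±0.20 if venue clustering has an ICC of 0.01 to 0.05. With a true effect of 10 points, more than half of such studies (26% + 33% = 59%) would point to a size wrong by a factor of two or more, or to none at all. At 20 points the share falls to about 26–28%.

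These shares rest on assumed uptake rates, full recruitment, no attrition and no clustering. Attrition or clustering would widen the interval for the difference. Bias from venue and participant choice is plausible and acknowledged in the article, but its size is unknown.

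On next steps the point is narrower: an increase in uptake is one of several joint considerations, and a non-randomised difference alone would not establish it.

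**What to change.** Replace the sentence in the sample-size paragraph with, for example: *The definitive study will be powered on a prespecified minimum important difference in screening uptake. This study will supply the comparison-group uptake, the recruitment rates and the six-month attrition.* Recruitment and attrition are already to be estimated, so nothing new has to be collected.

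Bring the sentence on exploratory tests in the Data analysis plan into line, and report the between-group difference with its 95% interval as descriptive and potentially confounded. That still serves the part of the Aim that concerns impact on uptake.

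In The intervention and in Value of the intervention, add that the non-randomised difference does not by itself establish an increase in uptake, and rest progression on feasibility and acceptability.

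Do not ask this study for a venue ICC to plan with. From a minimum of about 8 to 12 venues it would be as unusable as the difference itself.

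The cost is wording only. As of the June 2023 status note, hub data had still to be requested, so the change could still govern analysis and reporting. The downside is that the study no longer offers an effect estimate for planning, and the minimum important difference has to be agreed and justified separately.
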